**Fig. 1 Fig1:**
[figure not shown]
Schematic representation of the study design. MMF, mycophenolate mofetil; MP, methylprednisolone; pred, oral prednisolone; B, belimumab; R, rituximab; EoS, end of study; w, week

**Table 2 Tab2:** SPIRIT figure; overview of all measures

		Study period																				
			Evaluation visits																		EoS	FU
Timepoint (weeks)	**S**	**0**	**B**^**a**^	**2**	**4**	**6**	**8**	**12**	**16**	**22**	**28**	**36**	**44**	**52**	**60**	**68**	**76**	**84**	**92**	**100**	**104**	**116**
**Enrollment**																						
Eligibility screen	x																					
Informed consent	x																					
Allocation		x																				
**Interventions**																						
History	x		x	x	x	x	x	x	x	x	x	x	x	x	x	x	x	x	x	x	x	x
Physical examination	x		x	x	x	x	x	x	x	x	x	x	x	x	x	x	x	x	x	x	x	x
SBLA: hematology	x		x	x	x	x	x	x	x	x	x	x	x	x	x	x	x	x	x	x	x	x
SBLA: immunophenotyping	x		x	x	x	x	x	x	x	x	x		x	x	x	x	x	x	x	x	x	
SBLA: chemistry	x		x	x	x	x	x	x	x	x	x	x	x	x	x	x	x	x	x	x	x	x
SBLA: Ig/complement	x		x	x	x	x	x	x	x	x	x	x	x	x	x	x	x	x	x	x	x	
SBLA: autoantibodies	x		x	x	x	x	x	x	x	x	x	x	x	x	x	x	x	x	x	x	x	
SBLA: virus serology	x																					
Urine analysis + cytology	x		x	x	x	x	x	x	x	x	x	x	x	x	x	x	x	x	x	x	x	x
24h urine analysis	x		x		x			x			x		x		x		x		x		x	
Electrocardiogram	x																					
Chest x-ray	x																					
Kidney biopsy^b^	x																					
Blood product storage	x		x	x	x		x	x	x		x		x		x		x		x		x	
**Assessments**																						
SLEDAI/PGA	x		x	x	x	x	x	x	x	x	x		x	x	x	x	x	x	x	x	x	
SLICC damage score	x														x						x	
QoL questionnaire			x					x			x				x				x		x	
Treatment failure																					x	
Clinical and renal response											x										x	
Autoantibody reduction											x										x	
B cell depletion											x										x	
NET assay			x								x										x	

*S* screening, *B* baseline, *QoL* SF-36 quality of life questionnaire, *FU* follow-up, *SBLA* standard blood laboratory analysis, *Ig* immunoglobulins, *NET* neutrophil extracellular traps

^a^Baseline may be left out if planned within two weeks of screening. ^b^Kidney biopsy only in case of suspected renal involvement

Upon severe flares of SLE disease activity, alternative treatment options will be considered, which can result in the withdrawal of the subject from the study. Patients randomized to the standard-of-care treatment group can cross over to the intervention group in the case of either a severe flare or insufficient treatment response requiring a switch in medication. They will then be considered to have met the primary endpoint of treatment failure, will re-enter the study if they fulfill the inclusion criteria, and receive the complete study treatment of the intervention group as described above.

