**Methods:**

Synbiose 2 is a phase 3, multicenter, randomized, controlled, open-label 2-year clinical trial. Seventy adults with severe SLE including lupus nephritis will be randomized 1:1 to receive either standard of care consisting of prednisolone and mycophenolate as induction and maintenance treatment, or belimumab and rituximab combined with standard of care as induction treatment, followed by prednisolone and belimumab as maintenance treatment. The primary objective is to assess whether combined B cell therapy will lead to a reduction of treatment failure. Secondary endpoints are complete and partial clinical and renal response and the improvement of SLE-specific autoimmune phenomena. Safety endpoints include the incidence of adverse events, with a special interest in infections.

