### Study endpoints

The primary clinical endpoint is the proportion of patients with treatment failure during the trial period, defined as either death, development of end-stage renal disease, major renal or extrarenal flare, sustained doubling of serum creatinine, clinical or renal non-response, requiring induction therapy or plasmapheresis, requiring a dose reduction or discontinuation of mycophenolate—other than established by protocol—for more than 14 or 7 days respectively, discontinuation of belimumab for more than three consecutive doses, inability to complete two rituximab administrations, withdrawal for any reason, or loss to follow-up.

Secondary clinical endpoints will be evaluated at 28 and 104 weeks. Clinical response is defined as a reduction in SLEDAI of ≥ 4 points and no worsening of Physician Global Assessment (PGA) score of > 0.3 points on a scale of 0–3. Other secondary endpoints are clinical remission (defined as meeting the criteria of clinical response and additionally achieving to taper steroids to ≤ 5 mg/day), renal response (complete renal response being < 0,75gr proteinuria per 24 h and a serum creatinine within 125% of baseline), low-level disease activity (SLEDAI ≤ 4 with no activity in major organ systems, hemolytic anemia or gastrointestinal activity and no new disease, PGA ≤ 1 and ≤ 7.5mg prednisolone equivalent), and disease control (SLEDAI ≤ 2 with ≤ 5mg steroids per day) [36]. Patient-reported outcome measure includes the SF-36 Quality of Life questionnaire [37]. Other clinical secondary endpoints are feasibility and safety of combination treatment by monitoring the occurrence of adverse events, with special attention to infections.

The main immunological endpoint is reduction of anti-dsDNA and other disease-specific autoantibodies at 28 weeks, which is also assessed at 104 weeks. Secondary immunological endpoints are reduction of relevant autoantibodies, sustained B cell depletion, and regression of immune complex-mediated excessive NET production at 28 and 104 weeks.

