### Statistical analysis

The statistical analysis will primarily be performed on the intention-to-treat population. For non-biased immunological endpoints, a per-protocol analysis will be done to assess the pathophysiological effects of adding belimumab and rituximab onto standard of care. The observed rates of treatment failure will be displayed in survival curves and the difference between treatment groups will be assessed using a log-rank test.

Differences in baseline characteristics, immunological endpoints, and clinical response will be explored. The absolute and percentage reduction of autoantibody titers, memory B cells, and NET formation will be analyzed as continuous variables using the non-parametric Mann-Whitney *U* test to compare treatment groups. Clinical disease activity categorized by the aforementioned response criteria will be analyzed using the chi-square test for dichotomized variables. Dosages of immunosuppressants will be analyzed as continuous variables using Mann-Whitney *U* because of the limited number of patients. Missing data will be imputed as that subject’s previously observed value. Patients that have crossed over from the control group to the intervention group will be considered as having met the primary endpoint of treatment failure and will re-enter the study as a new subject. As such, they will be included in the intention-to-treat analysis. Also, they will serve as their own controls in an additional post hoc analysis.

Safety, toxicity, and adverse events will be documented, and the events considered to be at least possibly related to the study treatment will be summarized by severity and treatment group. Infectious AE’s will be presented to an independent infectious disease specialist for evaluation of severity and relation to study participation.

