Written informed consent will be obtained from all patients prior to the initiation of any study-specific procedure or data collection and includes consent for the use of participant data and specimens in potential follow-up studies. All data is stored in a standardized manner in an electronic data capture platform with restricted access. Data integrity is enforced through the following mechanisms. All data entry is carried out by a dedicated member of the research team. Source data will be kept on file at the participating sites and consistency checks against data stored in the database will be done at regularly scheduled monitoring visits. Documentation of changes will be available via audit trails. Patient privacy is ensured by de-identifying all data submitted to the electronic data capture platform and using subject identification codes. The chief investigator will have access to all data, and the other primary investigators will have access to the trial datasets of patients participating in their own medical centers. All patients will have the right to withdraw from the study at any time during the trial. It is of note that the possibility of crossing over in the case of a severe flare or insufficient response to standard of care increases the advantage of participation for patients, because this makes them eligible for a novel treatment strategy in a situation where treatment options may otherwise be limited. Follow-up evaluations will be performed for all patients at least 3 months after completing the 2-year follow-up and once a year thereafter if possible.

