Monitoring will take place two times a year and the monitoring process will be independent from the investigators. Auditing visits will take place as deemed necessary by the auditing committee. Severe adverse events will be reported to the sponsor within 24 h. A data monitoring committee was not necessary based on the risks of the study. However, to ensure subject safety, safety meetings with independent specialists will be held four times a year in order to monitor and evaluate adverse events, treatment failures, and drop-out. A clinical trial insurance that provides coverage for damage to research subjects through harm caused by the study is available in accordance with the legal requirements in The Netherlands. When medically indicated, trial visits can be intensified as desired or supplemented with the trial’s independent physician in the case of adverse events or harm that occurred during the trial. Additional health care needs that arise during or as a consequence of the trial will be adequately addressed by the investigators.

Several methods are employed to improve participant retention and completion of follow-up, minimizing the burden and practical implications for patients. Scheduling of appointments is planned well ahead of time and reminders are included. Travel allowance will be provided for unplanned visits to the study center. Furthermore, patients who are withdrawn from the study medication will be followed at regularly scheduled study visits as specified by the protocol, unless informed consent is withdrawn. Treatment during the study is defined up to 104 weeks, after which the treatment with belimumab can be continued or patients can be switched to another immunosuppressive regimen as preferred by the treating physician in shared decision with the patient. In the Netherlands, belimumab is covered by insurance companies for the treatment of LN patients posing no barrier to continue any medication from either treatment arm in routine clinical practice after completion of the study.

Significant protocol amendments will be communicated with all relevant parties. We will submit our findings for peer-reviewed, open-access publication, and data resulted from this randomized clinical trial as well as other related documentation will be available on reasonable request. This paper complies with the Standard Protocol Items: Recommendations for Interventional Trials (SPIRIT) recommendations for protocol reporting [39].

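### Rescue after a severe flare may end in withdrawal from the study, which conflicts with the article's own rule that patients off study medication stay on scheduled visits

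*Protocol article*

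**What the plan says.** The Study treatments section, in the paragraph after Table 2, deals with severe flares in both arms: "alternative treatment options will be considered, which can result in the withdrawal of the subject from the study". It then gives control patients a further route. After a severe flare or insufficient response they may cross over, and they re-enter the study if they meet the inclusion criteria.

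The retention paragraph under Ethical considerations and dissemination states the follow-up rule. Patients "withdrawn from the study medication will be followed at regularly scheduled study visits as specified by the protocol, unless informed consent is withdrawn". Withdrawn consent is the only exception given.

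Three other statements bear on the point:

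- Study endpoints counts "inability to complete two rituximab administrations, withdrawal for any reason, or loss to follow-up" as treatment failure. The same section says: "Secondary clinical endpoints will be evaluated at 28 and 104 weeks".
- Statistical analysis says: "Missing data will be imputed as that subject’s previously observed value".
- The abstract says: "Safety endpoints include the incidence of adverse events, with a special interest in infections".

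**The concern.** The two texts can apply to the same patient and give different answers. Suppose a flare calls for cyclophosphamide or another biological, which the Concomitant medication section prohibits throughout the study period. The patient then stops study medication and, under the retention paragraph, stays on scheduled visits. Under the flare clause the same patient may leave the study.

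An exit of that kind is triggered by outcome. Two things are at stake. Adverse events after rescue, infections in particular, could go unrecorded although they are a declared endpoint. And any week-104 secondary measure not taken at the flare would be filled with an earlier value, which could pre-date the flare that caused the exit.

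**Working it through.** **Are the two terms used as synonyms?** The article gives reason to think not. Its consent paragraph says: "All patients will have the right to withdraw from the study at any time during the trial". There the phrase means a patient's full exit. The primary endpoint lists withdrawal for any reason separately from interrupting mycophenolate or stopping belimumab. Leaving the study and leaving a drug are therefore different events elsewhere in the text.

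**Is the gap closed elsewhere?** The ethics section also promises follow-up of all patients at least 3 months after the 2-year follow-up is completed. That does not cover the time between a flare exit and week 104.

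**Who is exposed?** Control patients who cross over and re-enter remain under observation as new subjects. This leaves intervention patients, and control patients who do not cross over or do not meet the inclusion criteria for re-entry.

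**How old could a carried-forward value be?** Inputs are the columns of Table 2, read by position.

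| Measure | Scheduled at | Longest gap from week 12 on |
|---|---|---|
| 24h urine | screening, baseline, weeks 4, 12, 28, 44, 60, 76, 92, 104 | 16 weeks |
| SF-36 | baseline, weeks 12, 28, 60, 92, 104 | 32 weeks (28 to 60, 60 to 92) |
| SLEDAI/PGA | every visit from baseline to week 104 except week 36 | 16 weeks once (28 to 44), otherwise at most 8 |
| Chemistry (creatinine) | screening and every visit from baseline to week 116 | 12 weeks (104 to 116); at most 8 up to week 104 |

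Example for proteinuria: a patient flares and leaves just before week 44, with no extra collection. The last 24h urine is from week 28, almost 16 weeks before the exit. At week 104 it is 104 − 28 = 76 weeks old. Complete renal response needs proteinuria below 0.75 g per 24 h, so a pre-flare value could supply that component.

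Example for SF-36: a patient leaves just before week 60. The last questionnaire is also from week 28, almost 32 weeks before the exit, and again 76 weeks old at week 104.

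**How many patients?** The planned sample size is not in dispute. ln(1 − 0.54) / ln(1 − 0.23) = 2.97, the stated hazard ratio. Schoenfeld's formula with two-sided 5% alpha and 80% power gives 27 events, and 27 / 0.385 = 70.1, against the stated 70.

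Expected failures at the planning rates are 35 × 0.54 = 18.9 (control) and 35 × 0.23 = 8.05 (intervention), together 26.95 of 70. Withdrawal is itself a failure, so this total is a ceiling on flare exits among the 70 at those rates. It is not an estimate, because it also includes drug interruption, non-response and loss to follow-up.

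The share that would leave after rescue is not given. As an assumption only:

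- 10% of failures: 0.10 × 26.95 = 2.7 patients (4% of 70)
- 25%: 6.7 patients (10%)
- 50%: 13.5 patients (19%)

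**The case against.** The clause is permissive: it says what rescue can lead to and does not order an exit. It sits in a treatment section, and its author may have meant leaving the assigned regimen, in which case the retention rule already covers these patients. The article condenses a full protocol that may set out withdrawal procedures. All of this stands, and it limits how often the problem would arise. It does not remove the clause as printed, which allows something that the stated follow-up rule does not. The finding rests on two statements that are present, not on a missing detail.

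The harm is also narrower than it could look. Complete renal response additionally needs creatinine within 125% of baseline, and chemistry is run at every clinic visit. SLEDAI/PGA would often be scored close to the flare. Visits can be intensified when medically indicated, so an extra urine collection is possible, though not required. After a purely extrarenal flare, an older proteinuria value need not be wrong. Quarterly safety meetings review adverse events, treatment failures and drop-out, and the safety summary covers only events at least possibly related to study treatment. Neither provides for collecting events after a patient has left. An infection after the switch may still be judged possibly related to study drug given earlier.

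A reader might infer three stronger things that the documents do not support:

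- *The primary comparison is biased.* It is not affected by this route, since major flare and withdrawal both count as failure.
- *Every patient with a severe flare is lost.* The wording does not say so, and control patients who cross over and re-enter stay under observation.
- *The exit favours one arm.* Only control patients have the crossover route, but more control failures are planned. The net direction cannot be derived.

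**Conclusion.** The conflict between the flare clause and the retention rule is real and should be removed. Its reach is limited to adverse events after rescue and to the sparsely measured week-104 secondary values, chiefly 24h proteinuria and SF-36. It concerns intervention patients and control patients who do not cross over and re-enter. The number affected cannot be determined; the shares shown above are illustrations.

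The conclusion assumes that a site could apply the flare clause literally, that no extra assessment is made at the flare, and that the carry-forward rule is applied to the secondary endpoints as stated. The priority is minor to moderate.

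**What to change.** Three changes in wording:

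1. In the severe-flare sentence, replace the words on withdrawing the subject with: *discontinuation of study treatment, with scheduled visits and adverse-event collection continuing per Table 2 unless consent is withdrawn*.
2. State that control patients who cross over follow the re-entry schedule instead, so that nobody is on two schedules at once.
3. For the week-104 response endpoints, count patients rescued for a severe flare as non-responders. Neither a carried-forward value nor a value obtained on the rescue drug should make them responders. Keeping the visits does not settle this by itself: a patient who remits on rescue treatment would otherwise score as a response. SF-36 is not a response criterion, so its post-rescue values would be reported with a flag.

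The cost is a short amendment and visits that Table 2 already contains. A patient who stops study treatment after the week 28, 52 or 76 visit has 11, 8 or 5 visits left, counting week 116. Some visits will be for patients off study treatment. Values collected after rescue reflect the rescue drug as well as the assigned strategy and must be flagged. The sample size does not change.

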### Concomitant medication

Cotrimoxazole, antimalarials, intra-articular injections, NSAIDs, and statins can be initiated or continued during the study. Antiproteinuric agents are allowed at the discretion of the treating physician, according to the national guidelines.

Anti-TNF therapy, cyclophosphamide, and biologicals other than belimumab and rituximab are prohibited at any time during the study period and in the 60 days prior to day 0. Live vaccines are prohibited within 30 days prior to day 0. Any combination of mycophenolate with the following is not allowed: methotrexate, azathioprine, leflunomide, calcineurin inhibitors, sirolimus, 6-mercaptopurine, and thalidomide. Finally, any investigational agent outside of this study is prohibited.

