### Study treatments

All patients will be given standard of care consisting of 3 pulses of 500 mg (< 60 kg) or 1000mg (> 60 kg) of intravenous methylprednisolone. This will be followed by tapered oral prednisolone at a starting dose of 60mg daily together with mycophenolate at a starting dose of 500mg twice daily and increased weekly, titrated to achieve a target AUC of 60-90mg*h/L, with a maximum dose of 4000mg per day. In cases where therapeutic drug monitoring (TDM) is not possible, mycophenolate dose will be titrated against leukocyte counts and tolerability of the patient. Patients randomized to the intervention group will receive standard of care combined with self-administered subcutaneous belimumab 200mg weekly, and two doses of 1000-mg intravenous rituximab 4 and 6 weeks after belimumab initiation. One hundred-milligram intravenous methylprednisolone, 2-mg intravenous clemastine, and 1000-mg oral acetaminophen will be administered prior to rituximab infusions.

In both treatment groups, oral prednisolone will be tapered to 7.5mg before week 28 and to 5mg before week 52 and will be continued at a low dose for the remaining study period. Dose reduction to zero can be personalized to the tolerance of the patient, judged by the treating physician. In the control group, mycophenolate will be reduced by 50% at week 28 and continued for the remainder of the study period. In the intervention group, mycophenolate dose will be reduced by 50% at week 16 and discontinued at week 28. Belimumab will be continued throughout the entire study period. Consequently, after week 28, patients will enter the maintenance phase where they will receive either prednisolone and mycophenolate (control group) or prednisolone and belimumab (intervention group) (Fig. 1). Patients will be monitored closely during the study, with laboratory evaluation and study visits every 2 weeks during the first 8 weeks after inclusion, and increasingly longer intervals during the remainder of the study, up to 2 months eventually. An overview of study visits and assessments per visit is summarized in Table 2.

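### From week 28 the seven agents barred alongside mycophenolate are neither barred nor scored as failure in the intervention arm, while controls stay under the ban

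*Protocol article*

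**What the plan says.** Three parts of the protocol article's Methods bear on this.

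- **Concomitant medication** has two kinds of prohibition. One is unconditional: "Anti-TNF therapy, cyclophosphamide, and biologicals other than belimumab and rituximab are prohibited at any time during the study period". The other depends on mycophenolate being taken: "Any combination of mycophenolate with the following is not allowed: methotrexate, azathioprine, leflunomide, calcineurin inhibitors, sirolimus, 6-mercaptopurine, and thalidomide".
- **Study treatments** ends mycophenolate at different times. For one arm, "In the intervention group, mycophenolate dose will be reduced by 50% at week 16 and discontinued at week 28". For the other, "In the control group, mycophenolate will be reduced by 50% at week 28 and continued for the remainder of the study period". From then on "they will receive either prednisolone and mycophenolate (control group) or prednisolone and belimumab (intervention group").
- **Study endpoints** defines treatment failure. Its components on disease activity and re-treatment include "major renal or extrarenal flare, sustained doubling of serum creatinine, clinical or renal non-response, requiring induction therapy or plasmapheresis". It also counts an unplanned mycophenolate reduction of more than 14 days or stop of more than 7 days, prolonged belimumab interruption, an incomplete rituximab course, withdrawal and loss to follow-up. Starting a further immunosuppressant is not on the list.

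The text after Table 2 adds that a control with a severe flare, or with an insufficient response that requires a change of drug, may cross over and is then a treatment failure. Table 2 schedules clinical and renal response only at weeks 28 and 104.

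**The concern.** The strategy under test is whether belimumab with prednisolone can replace mycophenolate in maintenance. That replacement takes place after week 28, which is when the rule on the seven agents stops applying to one arm.

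Take two patients whose disease worsens to the same degree in that period, short of a major flare. The control cannot be given one of the listed agents on top of mycophenolate, and a switch to one of them means coming off mycophenolate, which scores after 7 days. The intervention patient can be given the same agent on top of belimumab, and nothing in the composite scores that step. If the added drug works, the patient may also be a responder at week 104, so the non-response component does not pick up the episode either.

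The trial is open-label, so the physician who chooses the add-on knows the arm. Failures removed in this way would be credited to the allocated strategy in the primary log-rank test.

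**Working it through.** **1. The rules side by side, weeks 28 to 104**

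| Event | Control | Intervention |
|---|---|---|
| On mycophenolate by protocol | Yes, at half dose | No |
| Listed agent prohibited | Yes | No express rule |
| Anti-TNF, cyclophosphamide, other biologicals prohibited | Yes | Yes |
| Patient moved to a listed agent | Scores (mycophenolate off for more than 7 days) | Add-on to belimumab does not score in itself |
| Major flare, non-response, induction therapy, withdrawal | Scores | Scores |

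The window is 104 − 28 = 76 weeks, and 76/104 = 73%. The 104 weeks come from the statement "Treatment during the study is defined up to 104 weeks".

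**2. The plan's own sample size**

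Inputs from Sample size calculation: failure of 54% and 23%, 5% alpha (two-sided assumed), 80% power.

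- Hazard ratio = ln(0.46)/ln(0.77) = 2.97, as stated.
- Schoenfeld events = 4 × (1.96 + 0.84)² / (ln 2.97)² = 26.5, rounded up to 27.
- Patients = 27 / 0.385 = 70.1, against 70 stated. The figure is reproduced.
- Power with 35 per arm: expected events are 35 × (0.54 + 0.23) = 26.95, which gives 80.7%.

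**3. How much of the endpoint falls in the window**

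Assume a constant hazard: −ln(0.46)/104 = 0.00747 per week.

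- Failure by week 28 = 1 − exp(−28 × 0.00747) = 18.9%.
- Failure after week 28 = 54% − 18.9% = 35.1%. That is 65% of all failures, or about 12 of 35 patients.
- At the planned 23%, about 70% of failures fall after week 28 (5 to 6 of 35).

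**4. Illustration of the bias**

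Assume equal true failure of 54% in both arms, 35 per arm and constant hazard. A share f of post-week-28 intervention failures is averted by unscored add-ons. Observed intervention failure = 54% − f × 35.1%. The last column is the simulated chance (20,000 runs per row) of a log-rank result that favours the intervention at two-sided 5%.

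| f (assumed) | Observed intervention failure | False positive in its favour |
|---|---|---|
| 0 | 54% | 2.5% |
| 10% | 50% | about 5% (4.6%) |
| 25% | 45% | about 10% |
| 50% | 36% | about 26% |

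**5. Power if the start of such agents is scored**

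Suppose k intervention patients fail on this ground beyond the planned 23%, with no change among controls. Then p = 0.23 + k/35, HR = ln(0.46)/ln(1 − p), d = 35 × (0.54 + p), and power = Φ(√(d/4) × ln HR − 1.96).

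| k | p | HR | Power |
|---|---|---|---|
| 0 | 23.0% | 2.97 | 81% |
| 1 | 25.9% | 2.60 | 71% |
| 2 | 28.7% | 2.29 | 61% |
| 3 | 31.6% | 2.05 | 50% |

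**The case against.** Much of the defence is sound, and it sets the limits of the point.

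- **Most serious rescue already scores.** A reader might infer that intervention patients can receive any rescue for 76 weeks without failing. The composite does not support that: major flare, non-response, creatinine doubling, induction therapy, plasmapheresis and withdrawal all count. The strongest options also stay prohibited in both arms throughout.
- **Silence is not permission.** Study treatments names prednisolone and belimumab as the maintenance regimen, and none of the seven agents is among the drugs that Concomitant medication says may be started or continued. An add-on would depart from the described strategy. A reader might call this a contradiction; it is better described as unreconciled, because the regimen is named without additions being barred.
- **Controls may have an unscored route too.** The composite counts mycophenolate reductions and stops, not increases, so raising the dose again after the week-28 cut is not listed. Conversely, Table 1 speaks of induction by switching to or increasing mycophenolate, so an intervention patient's restart for active disease may already count as induction therapy. The text does not settle either case, and it cannot be said that only the intervention arm loses failures.
- **The shares are assumed.** They are applied to all late failures, although death, loss to follow-up and belimumab interruption would hardly be prevented by an add-on.
- **The article is condensed.** The full protocol, at version 10, may hold a further rule.

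What remains is not a mere omission. The article states both the prohibition and the composite, and read together they treat the start of a listed agent differently by arm.

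**Conclusion.** The point holds in a limited form. From week 28 to week 104 the seven listed agents or classes are neither expressly prohibited nor counted as failure in the intervention arm. Controls remain under the prohibition, and for them leaving mycophenolate is a failure. The gap concerns add-ons for worsening below the scored thresholds, or add-ons early enough to prevent a scored event.

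The likely direction is towards the intervention. The 76 weeks are firm. The size of the bias cannot be derived from the documents. The 5% to 26% range rests on a constant hazard, equal true failure of 54% and an averted share of 10% to 50% that has no source in the article. A reader might take the upper figure as the trial's actual error rate; nothing in the documents supports that.

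**What to change.** 1. Reconcile Study treatments, Concomitant medication and Study endpoints, so that the status of the listed agents after week 28 is explicit for each arm. Which drugs are allowed is for the sponsor to decide.
2. In the composite, score the start of any immunosuppressant outside the allocated regimen as treatment failure on its start date, identically in both arms.
3. State how a mycophenolate restart after week 28 (intervention) and a re-escalation after the 50% cut (control) are handled for the endpoint, so that neither arm has an unscored escalation route.
4. If the primary endpoint of the ongoing trial is not to be amended, pre-specify items 2 and 3 as a sensitivity analysis of it.

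**Cost.** Start dates can be taken from concomitant-medication records, so little new data collection should be needed. Recruitment began in November 2018, however, so changing a primary-endpoint component of a running open-label trial needs a formal amendment before analysis. More failures will be scored, mainly in the intervention arm, and power falls as shown in the working. The sensitivity-analysis route leaves the primary endpoint and its planned power untouched, but also leaves the primary result open to this bias.
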